## Abstract

**Background:**

Trials failed to demonstrate additional value of completion axillary lymph node dissection in case of limited sentinel lymph node metastases in breast cancer patients undergoing breast conserving therapy. It has been suggested that the low regional recurrence rates in these trials might partially be ascribed to accidental irradiation of part of the axilla by whole breast radiation therapy, which precludes extrapolation of results to mastectomy patients. The aim of the randomized controlled BOOG 2013–07 trial is therefore to investigate whether completion axillary treatment can be safely omitted in sentinel lymph node positive breast cancer patients treated with mastectomy.

**Design:**

This study is designed as a non-inferiority randomized controlled multicentre trial. Women aged 18 years or older diagnosed with unilateral invasive clinically T1-2 N0 breast cancer who are treated with mastectomy, and who have a maximum of three axillary sentinel lymph nodes containing micro- and/or macrometastases, will be randomized for completion axillary treatment versus no completion axillary treatment. Completion axillary treatment can consist of completion axillary lymph node dissection or axillary radiation therapy. Primary endpoint is regional recurrence rate at 5 years. Based on a 5-year regional recurrence free survival rate of 98 % among controls and 96 % for study subjects, the sample size amounts 439 per arm (including 10 % lost to follow-up), to be able to reject the null hypothesis that the rate for study and control subjects is inferior by at least 5 % with a probability of 0.8. Results will be reported after 5 and 10 years of follow-up.

**Discussion:**

We hypothesize that completion axillary treatment can be safely omitted in sentinel node positive breast cancer patients undergoing mastectomy. If confirmed, this study will significantly decrease the number of breast cancer patients receiving extensive treatment of the axilla, thereby diminishing the risk of morbidity and improving quality of life, while maintaining excellent regional control and without affecting survival.

**Trial registration:**

The BOOG 2013–07 study is registered in the register of ClinicalTrials.gov since April 10, 2014, Identifier: NCT02112682.

**Electronic supplementary material:**

The online version of this article (doi:10.1186/s12885-015-1613-2) contains supplementary material, which is available to authorized users.

## Background

For a long time the standard procedure to assess the axillary lymph node status in breast cancer was an axillary lymph node dissection (ALND). This operation is associated with significant morbidity and a decrease in quality of life [1, 2]. The therapeutic benefit of this operation – improving overall survival and maintaining regional control – has been questioned in several trials.

The NSABP B-04 trial was initiated in 1971 and randomized clinically node negative breast cancer patients to radical mastectomy, mastectomy followed by axillary radiation therapy, or mastectomy followed by a delayed ALND after the development of palpable lymphadenopathy during follow-up [3]. The ALND specimen of patients in the radical mastectomy group contained lymph node metastases in 40 % of the patients. Nevertheless, this trial demonstrated that omitting primary axillary treatment of occult positive lymph nodes in patients with a clinically node negative status did not affect distant disease free- and overall survival, even after 25 years of follow-up and without the use of adjuvant systemic or radiation therapy. A delayed ALND was performed in 18.6 % of the patients in the mastectomy-only group, which is less than half of the patients with occult positive lymph nodes based on the radical mastectomy group [3]. The ‘wait-and-see’ policy therefore prevented axillary overtreatment in the majority of patients. Despite these favourable results, ALND remained to be the standard procedure to assess the axillary lymph node status, partly due to adjuvant systemic therapy that appeared to be mainly beneficial for node-positive breast cancer patients.

In the past 15 years, the sentinel lymph node biopsy (SLNB) has become the standard, less invasive technique for nodal staging of clinically node negative breast cancer patients [4]. A completion ALND was, until recently, routinely performed in patients with a metastasis in the sentinel lymph node (SLN) [5].

The AMAROS trial demonstrated that axillary and periclavicular radiation therapy could safely replace completion ALND in patients with clinically T1-2 breast cancer, no palpable lymphadenopathy and a positive SLN, without compromising the 5-year regional recurrence rate, disease free- and overall survival [6]. Patients in the AMAROS trial were treated with breast conserving therapy in 82 %, with mastectomy in 18 %, and adjuvant systemic therapy in 90 % of the cases. At five years, a significant lower lymphedema rate based on arm circumference measurements was observed, favouring the radiation therapy group.

Two recent trials further suggest that completion ALND might be safely omitted [7, 8]. The ACOSOG Z0011 trial randomized patients with clinically T1-2 breast cancer, no palpable lymphadenopathy and 1–2 macrometastatic SLNs, who were treated with breast conserving therapy, to completion ALND or watchful waiting [7]. The ALND specimen of 27 % of the patients in the completion ALND group contained additional lymph node metastases beyond the SLN, but omitting the completion ALND in the watchful waiting arm did not result in an inferior regional recurrence rate, disease free- or overall survival [7, 9]. Findings of the ACOSOG Z0011 are supported by results of the IBCSG 23–01 trial, which revealed that further axillary treatment can be safely omitted after the detection of a micrometastasis in the SLN [8]. All patients in the IBCSG 23–01 trial had a clinically T1-2 status and no palpable lymphadenopathy, 91 % was treated with breast conserving therapy, 9 % with mastectomy and 97 % with adjuvant systemic therapy.

The clinically node negative patients in the AMAROS, ACOSOG Z0011 and IBCSG 23–01 trial were selected by physical examination of the axilla. In the Netherlands, an axillary ultrasound next to physical examination is routinely performed for preoperative lymph node staging, combined with tissue sampling in case of a suspicious lymph node [5]. The ESMO breast cancer guideline also describes that an ultrasound of the regional lymph nodes should be included in the diagnostic work-up of breast cancer patients, and recommends not to perform an SLNB when axillary lymph node involvement is proven on ultrasound-guided biopsy [10]. The accuracy of physical examination of the axilla for preoperative lymph node staging is low, with a sensitivity of up to 32 % for detecting axillary metastases [11, 12]. The sensitivity of axillary ultrasound combined with tissue sampling if indicated is 50–55 % [13, 14]. Furthermore, patients with a more favourable tumour load are selected when an axillary ultrasound is performed, as the total number of nodal metastases is significantly lower after a negative axillary ultrasound than after negative physical examination [15]. In addition, a negative axillary ultrasound accurately excludes advanced nodal disease (≥4 lymph node metastases) with a negative predictive value of 93–96 % [16, 17]. The performance of an axillary ultrasound for preoperative nodal staging might therefore be beneficial when incorporating the omission of completion axillary treatment in patients with SLN metastases into daily practice [18].

The AMAROS, ACOSOG Z0011 and IBCSG 23–01 trial were underpowered, as events occurred less common than anticipated [6–8]. Low regional recurrence rates in the study arms of these trials of 1.0 %, 0.9 % and 1.1 %, respectively, might be due to treatment of most patients with breast conserving therapy and adjuvant systemic therapy. Whole breast radiation therapy in the context of breast conserving therapy is known to decrease the regional recurrence rate, most likely caused by accidental irradiation of part of the axilla [19–21]. However, biology and systemic therapy also play a role in achieving low regional recurrence rates. The NSABP B-04 trial demonstrated that less than half of the patients with occult nodal metastases develop clinically detectable lymph nodes, while none of the patients received adjuvant systemic therapy [3]. Reported pathologic complete response rates for axillary lymph node metastases following primary systemic therapy of up to 40 %, demonstrate that systemic therapy can eradicate lymph node metastases [22, 23].

The non-inferior regional recurrence-, disease free- and overall survival rates in the ACOSOG Z0011 and IBCSG 23–01 trial imply that extensive surgical treatment of lymph node metastases with a completion ALND is not of added value for breast cancer patients with a clinically T1-2 status, no palpable lymphadenopathy, limited SLN metastases, who are treated with breast conserving therapy and adjuvant systemic therapy [7, 8]. Results of the ACOSOG Z0011 and IBCSG 23–01 trial cannot be extrapolated to SLN positive patients treated with mastectomy, as these patients do not routinely receive adjuvant radiation therapy.

Therefore, we propose the randomized controlled BOOG 2013–07 trial to prove that completion axillary treatment can be safely omitted in breast cancer patients with a clinically T1-2 status, a negative axillary ultrasound and limited SLN metastases, who are treated with a mastectomy. We aim to decrease the number of breast cancer patients receiving overtreatment of the axilla, to diminish the risk of morbidity and to improve quality of life, while maintaining excellent regional control and without affecting survival.

### Main study objectives

The main aim of the BOOG 2013–07 study is to investigate whether omitting completion axillary treatment is non-inferior to completion axillary treatment in terms of the 5 and 10-year regional recurrence rate, in breast cancer patients with a clinically T1-2 status, a negative axillary ultrasound and limited SLN metastases, who are treated with a mastectomy. Secondary objectives that are assessed during a follow-up of 10 years include the assessment of quality of life, distant-disease free survival, overall survival, local recurrence rate, contralateral breast cancer, administration of adjuvant radiation therapy, and delayed axillary treatment.

## Methods

### Study design

The BOOG 2013–07 is a Dutch non-inferiority randomized controlled multicentre trial. Patients with clinically T1-2 invasive breast cancer, negative axillary ultrasound and limited SLN metastases, who are treated with mastectomy, are randomized to completion axillary treatment or no completion axillary treatment. Outcome will be evaluated after 5 and 10 years of follow-up. This study will be performed in 43 centres in the Netherlands. The study was conducted in accordance to the standards of Good Clinical Practice, in agreement with the Declaration of Helsinki and with Dutch law in general and with the Medical Research Involving Human Subjects Act (in Dutch: Wet Medisch-wetenschappelijk Onderzoek met mensen) in particular. This study was approved by the medical ethics committee of the Netherlands Cancer Institute - Antoni van Leeuwenhoek Hospital (PTC14.0032/M14CAT). The Board of Directors approved initiation of the study in current participating centres that are open for accrual (Additional file 1). The BOOG 2013–07 trial is registered at ClinicalTrials.gov (NCT02112682).

### Study population

Women aged 18 years or older diagnosed with clinically T1-2 N0 invasive breast cancer, who are treated with a mastectomy and who have a minimum of one micrometastatic and a maximum of three macrometastatic axillary SLNs, are eligible for inclusion. Clinically N0 is defined as no signs of axillary lymph node metastases at physical examination and preoperative axillary ultrasound (or negative cyto-/histopathology). Primary systemic therapy and primary and secondary breast reconstructions are allowed.

Exclusion criteria include the following: SLNs containing only isolated tumour cells (<0.2 mm); solitary parasternal SLN metastasis; bilateral breast cancer; evidence of metastatic disease; history of invasive breast cancer; previous treatment of the axilla with surgery or radiation therapy (except surgery for hidradenitis suppurativa or for other superficially located skin lesions, such as naevi); pregnancy or lactation; other prior malignancies, except successfully treated malignancies that occurred more than five years before randomization, and except successfully treated basal cell and squamous cell skin cancer, and carcinoma in situ of the breast or cervix.

#### Axillary ultrasound

Axillary ultrasound is standard of care in the Netherlands for preoperative nodal staging of breast cancer patients [5]. The following criteria are used during ultrasound of axillary level 1–3 to identify positive lymph nodes: long to short axis ratio of <2 (i.e. round), diffuse or focal cortical thickening, effacement or replacement of the fatty hilum, and/or nonhilar blood flow (using Doppler ultrasound, if detectable). As described in the Dutch breast cancer guideline, cortical thickening of more than 2.3 mm is considered as the optimal cut-off point to perform fine-needle aspiration biopsy [5]. Additionally, a subjective assessment of thickening can be made by the radiologist during real-time imaging, similar to the studies by Koelliker et al., Abe et al., and Neal et al. [16, 24, 25]. Fine-needle aspiration biopsy or core biopsy is recommended when suspicious lymph nodes are identified. In case of two or more abnormal lymph nodes, the lymph node with the most suspicious findings is selected for tissue sampling.

#### Sentinel lymph node biopsy

For the SLNB, Technetium-99 m Nanocolloid will be injected into breast parenchymal tissue surrounding the tumour, biopsy cavity or periareolar, followed by lymphoscintigraphic images. The SLN (s) will be identified during surgery by using the following triple technique: lymphoscintigraphic images, blue dye and a gamma probe. Palpation of the axilla after removal of the SLN (s) is performed to identify and remove suspicious (non-) SLN (s).

As a minimal requirement for pathological assessment, each SLN is examined at three histological levels (500-μm intervals). On each level two parallel sections are performed, one for haematoxylin and eosin (H&E) staining and one for immunohistochemical (IHC) staining. IHC staining is done only when H&E staining is negative, and is performed for markers containing at least cytokeratin 8 and 18 (e.g. CAM 5.2, NCL5D3). Lymph nodes submitted for pathological examination, which are marked by the surgeon as non-SLNs are examined with H&E and if negative with cytokeratin IHC staining. The exact diameter of each metastasis must be determined, as well as describing the occurrence of extranodal growth. Isolated tumour cells (<0.2 mm) are considered as SLN negative.

#### Mastectomy

A mastectomy is defined as the surgical removal of all glandular breast tissue. The size of the primary tumour is determined during pathological assessment. The hormone receptor status is determined by IHC staining and is considered positive if ≥10 % of the cells stain positive. HER2neu status is determined by IHC and in case of 2+ determined by CISH or FISH. Histological tumour grading is assessed according to the modified Bloom-Richardson grading system. The presence of multifocality is defined as foci or carcinoma separate from the primary tumour. The histological tumour type is defined according to the World Health Organization. Presence of lymphovascular invasion is defined as one or more tumour cells in a lymphatic or vascular structure.

The modified Bloom-Richardson grading system consists of three components of the tumour morphology and a score of 1, 2 of 3, is assigned to each of these components: the extent of tubule formation (1 = >75 %; 2 = 10–75 %; 3 = <10 %), the nuclear polymorphism (1 = comparable to normal epithelium; 2 = enlarged, vesicular, small nucleoli; 3 = polymorphic, vesicular, large nucleoli) and mitotic activity defined as the number of mitoses per 2 mm^2^ (1 = 0–7 mitoses per 2 mm^2^; 2 = 8–12 mitoses per 2 mm^2^; 3 = ≥13 mitoses per 2 mm^2^). The histological grade is determined by the sum of these scores, with grade I for the scores 3–5, II for 6–7, and III for 8–9.

### Consent and randomization

Eligible patients will be informed about the study aims, study procedures, possible adverse events, mechanism of treatment allocation, and their rights and responsibilities. After written informed consent is obtained, patients will be randomized between completion axillary treatment (control arm) and no completion axillary treatment (study arm).

Stratification factors for randomization include the following: age (≤50, 50 ≤ 75, >75), oestrogen receptor status (positive vs. negative), HER2neu status (amplified vs. not-amplified), lymph node metastasis (micro- vs. macrometastasis), clinical tumour size prior to any treatment (<3 cm vs. ≥3 cm), grading (grade I-II vs. III - according to modified Bloom-Richardson grading system), primary systemic therapy and participating centre.

### Completion axillary treatment

Completion axillary treatment in the control arm can consist of a completion ALND or axillary radiation therapy in accordance to the Dutch breast cancer guideline [5]. Axillary radiation therapy can either be of axillary level 1 and 2 (i.e. the regions that would be operated upon if an ALND would be performed), or radiation therapy of axilla level 1–3 and periclavicular nodes (i.e. conform the regions that were irradiated in the AMAROS trial). Each participating centre states on beforehand which radiation strategy they follow for which patient categories.

### Radiation therapy

#### Chest wall irradiation

Radiation therapy of the chest wall after mastectomy is indicated in specific circumstances depending on the Dutch and local protocols and therefore not an exclusion criterion in this study. According to the Dutch breast cancer guideline, postoperative radiation therapy after mastectomy can be considered in patients with 1–3 axillary lymph nodes containing metastatic disease with at least one risk factor. Risk factors include angioinvasive growth, grade III tumours, tumour size of ≥3 cm and/or age ≤ 40 years [5]. The indications for radiation therapy will be clearly defined for each participating centre to prevent a low-threshold for chest wall irradiation in study arm B.

#### Dose and fractionation for chest wall and axilla

A fractionation scheme equivalent to 25 × 2 Gy, 5 fractions per week is applied; i.e. schemes of 15–16 × 2.66 Gy, 5 fractions per week are allowed as well. In case of an irradical resection a boost is given to the tumour bed, equivalent to 7–13 × 2 Gy. A simultaneous integrated boost is recommended, with high fraction size not exceeding 2.67 Gy.

#### Delineation of chest wall and axilla

Delineation of target volumes is performed using the ESTRO guidelines of Offerson et al. [26]. Delineation of all target volumes, including the thoracic wall and heart and lungs is obligatory. Delineation of other normal structures is optional. To allow adequate evaluation of the radiation in the axillary nodal regions, delineation of axillary level 1, 2, Rotter nodes, 3 and 4 is obligatory, also in case of chest wall irradiation alone.

#### Radiation technique and dose distribution

The dose in the Planning Target Volume of the chest wall with or without axillary and periclavicular nodes must be between 95–107 % of the prescribed dose. If the distance between the skin and the pectoral muscle is < 5 mm, it is allowed to use tissue-equivalent material to increase the superficial dose. The mean lung dose should be < 5 Gy in case of tangential fields only, and < 7.5 Gy in case of locoregional irradiation. The heart volume receiving > 25 Gy should be < 20 %; the Mean Heart Dose should preferably be below 3 Gy, and should certainly not exceed 5 Gy. If lung or heart constraints cannot be met, some underdose in the thoracic wall target volume can be accepted to reach the constraints, provided that the quadrant where the primary tumour was localized is adequately covered. Respiratory control techniques to reduce heart dose are highly recommended for left sided breast cancer patients. The dose in the brachial plexus should be kept below an equivalent of 60 Gy in 30 fractions. The minimum, maximum and mean dose of the axilla level 1, 2, Rotter nodes, 3 and 4 must always be recorded for evaluation purposes, even in case only chest wall radiation therapy is applied.

### Systemic therapy

The indication for systemic therapy is determined for the individual patient according to the Dutch breast cancer guideline and multidisciplinary approach. Primary systemic therapy in clinically T1-2 (pre-systemic therapy) patients is no exclusion criterion.

### Follow-up

During the 10-year follow-up period, outpatient clinic visits take place annually with physical examination of the axilla. A mammography is performed annually in the first five years of follow-up. In year six to ten, a mammography is performed annually in patients aged ≤60 years or once every two years in patients aged >60 years. Additional diagnostic imaging is performed on indication. An axillary ultrasound is performed in patients with a clinical suspicion of axillary lymph node metastases during follow-up. If an axillary lymph node metastasis is confirmed by tissue sampling, staging for distant metastatic disease is performed in accordance to the Dutch breast cancer guideline. In patients with a clinical suspicion of distant metastatic disease during follow-up, staging for metastatic disease is performed, in combination with physical examination of the axilla for the detection of possible axillary lymph node metastases, followed only by an axillary ultrasound in patients with a clinical suspicion of axillary lymph node metastases.

### Quality of life

Quality of life will be assessed with a set of questionnaires. The first set is provided pre-randomisation for baseline measurement, and the following are provided sequentially post-randomization at 6 months, and at 1, 2, 5 and 10 years. Patients are eligible for evaluation only when at least the pre-randomisation questionnaire and the subsequent questionnaire is completed. The set of questionnaires consist of the EORTC QLQ-C30 and QLQ-BR 23 questionnaire, the Lymph-ICF, STAI-trait and NEO-FFI questionnaire [27–30]. The combination of these questionnaires will provide information on the general and breast cancer specific quality of life, subjective morbidity, and anxiety and personality traits that might influence the outcome of quality of life [31].

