### Statistics

#### Endpoints

Regional recurrence rate is the primary endpoint in this study. Secondary endpoints include number of delayed axillary treatment, distant-disease free survival, overall survival, local recurrence rate, other-regional recurrence rate, contralateral breast cancer rate, percentage difference in the administration of postoperative radiation therapy, axillary morbidity rate and quality of life. The events included in the definitions of the different recurrences are provided in Table 1, and are based on the Maastricht Delphi Consensus on Event Definition by Moossdorff et al. [32, 33]. Pathological confirmation of a regional recurrence is mandatory, and recommended in case of other suspicious lesions. All cases with a lesion that is highly suspicious for tumour recurrence on imaging, but not accessible for tissue sampling are presented to the Data Safety Monitoring Board (DSMB) for an independent review.

**Table 1 Tab1:** Definition of a regional, other-regional, local and distant recurrence

Classification	Events included
Regional recurrence	Recurrence in an ipsilateral axillary-, infraclavicular-, or supraclavicular lymph node
Other-regional recurrence	Recurrence in an ipsilateral internal mammary lymph node
Local recurrence	Recurrence in skin or subcutaneous tissue on the ipsilateral chest wall
Distant recurrence	Recurrence in any other location, including recurrence involving the
	sternal bone, or contralateral lymph nodes

Time to event endpoints are defined as the time interval between the date of randomization and the date of first suspicion of the predefined recurrence, or the date of death, whichever comes first, measured in days. Patients in whom recurrence is not observed and are still alive are censored at the date of last follow-up. Death from breast cancer and its treatment, death from a second primary invasive non-breast cancer, and death from other- or an unknown cause are recorded.

Administration of postoperative radiation therapy is registered and the percentage difference between both study arms is recorded. Axillary morbidity rate will be assessed using a validated questionnaire and by predefined adverse events that are recorded by the treating physician. Quality of life will be assessed using validated questionnaires.

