#### Sample size

Prior data indicate a 5-year regional recurrence free survival rate of 98 % for the control patient group, and a regional recurrence free survival rate of 96 % is expected for the experimental patient group. A difference of no more than 5 % (delta = 5 %) is considered acceptable, when taking in account the higher morbidity rate caused by completion axillary treatment in the control arm. The expected regional recurrence free survival rates and delta result in a sample size of 399 per arm. Therefore, we will need to study 399 experimental subjects and 399 control subjects to be able to reject the null hypothesis that the rate for experimental and control subjects is inferior by at least 5 % with a probability of 0.8. When taking in account a lost to follow-up rate of 10 %, 878 patients need to be randomized. An annual accrual of 324 patients can be achieved, based on the incidence of women diagnosed with invasive breast cancer in the Netherlands, the rate of patients that is operated on primarily (excluding patients treated with chemo- or hormonal therapy only, or with metastatic disease and frail elderly), the rate of patients with a positive SLN, treatment with mastectomy, the 43 participating hospitals, and an expected accrual rate of 30 %. Therefore, three years will suffice to include the 878 patients.

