#### Final analysis

Primary and secondary endpoints will be analysed per protocol and in the intention to treat population after 5 and 10 years of follow-up. Primarily, uncorrected chi-squared statistics will be used to evaluate the null hypothesis. The chi-square test will be based on the Kaplan-Meier estimator, in case of censored data. Additionally, cox proportional hazards models and Kaplan Meier estimates will be used to analyse the outcome of both groups and to assess the univariable and multivariable association between prognostic variables, treatment and events, using the stratification factors. All statistical tests are 1-sided and a *P* value of 0.05 or less is considered statistically significant.

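### Quality of life is evaluated only in patients with the baseline and the next (most naturally the 6-month) questionnaire, a post-randomisation exclusion that loses later data and can bias the arm comparison

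*Protocol article*

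**What the plan says.** The Quality of life section of the protocol article places the first questionnaire set before randomisation; after that, "the following are provided sequentially post-randomization at 6 months, and at 1, 2, 5 and 10 years". It then fixes who counts: "Patients are eligible for evaluation only when at least the pre-randomisation questionnaire and the subsequent questionnaire is completed".

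The Endpoints section lists "axillary morbidity rate and quality of life" among the secondary endpoints. It adds: "Axillary morbidity rate will be assessed using a validated questionnaire and by predefined adverse events". So questionnaire data also feed a second endpoint.

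The Final analysis section sets the analysis populations: "Primary and secondary endpoints will be analysed per protocol and in the intention to treat population after 5 and 10 years of follow-up". It makes no exception for quality of life, and nothing else in the article reconciles the two statements.

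**The concern.** The rule has two halves of different weight. The baseline form precedes randomisation. Requiring it costs patients and precision but does not by itself disturb the randomised comparison. The next form in the sequence is due six months after randomisation, and whether it comes back may depend on what has happened to the patient since then.

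Such dependence is plausible here. The control arm receives axillary dissection or axillary radiotherapy and the study arm receives neither, so patients will know their arm. The Sample size section itself expects more morbidity in the control arm, and the Adverse events section lists early problems such as seroma, wound complications and reduced shoulder movement. Selecting patients on the 6-month form may then select differently in the two arms.

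The stake is the credibility of the quality-of-life comparison at 1, 2, 5 and 10 years. Better quality of life is a stated aim of omitting completion treatment (Background, and the Discussion paragraph of the Abstract). If the rule also governs the questionnaire used for axillary morbidity, that part of the morbidity endpoint is exposed as well.

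**Working it through.** **Reading the rule.** The schedule is sequential: baseline, 6 months, 1, 2, 5 and 10 years. The rule refers to one subsequent questionnaire, in the singular, directly after that schedule. The natural reading is the 6-month form. A patient with forms at baseline, 1, 2, 5 and 10 years but none at 6 months is then not evaluable.

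**Inputs.** The article gives no figure for quality of life, so there is none to reproduce. The only number taken from it is the 878 patients to be randomised (Sample size). All return rates below are assumptions.

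**Upper bound on the loss.** Let m be the share missing the 6-month form, and suppose all of them return a given later form.
- m = 10%: 878 × 0.10 = 88 patients lost; standard error ratio 1/√0.90 = 1.054.
- m = 20%: 878 × 0.20 = 176 patients lost; standard error ratio 1/√0.80 = 1.118.

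**If early non-responders also tend to miss later forms.** Suppose only half of them return the later form and all other patients do.
- m = 10%: 88 × 0.5 = 44 forms discarded; kept/available = 0.90/0.95 = 0.947; ratio 1/√0.947 = 1.03.
- m = 20%: 176 × 0.5 = 88 forms discarded; kept/available = 0.80/0.90 = 0.889; ratio 1/√0.889 = 1.06.

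**Size of the evaluable set.** Assume independent completion of 80% to 95% at baseline and 70% to 90% at 6 months.
- Lowest: 878 × 0.80 × 0.70 = 492 (56%).
- Highest: 878 × 0.95 × 0.90 = 751 (86%).
- Patients who completed baseline and are excluded only for the 6-month form: from 878 × 0.80 × 0.10 = 70 to 878 × 0.95 × 0.30 = 250.

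**Bias, by simulation with no true arm difference.** Assumptions: 439 per arm, score SD 20, within-patient correlation 0.7² = 0.49, 90% baseline completion, about 80% 6-month completion, 85% 12-month completion unrelated to score, 1,500 replicates. The slope is the change in log-odds of returning the 6-month form per SD of the 6-month score. Bias is the mean 12-month difference, second arm minus first, under the rule and with all available 12-month forms.
- Slopes 0 and 0: 0.05 under the rule; 0.03 with all forms.
- Slopes 0.5 and 0.5: −0.03; −0.04.
- Slopes 0.5 and 0: −0.94; 0.04.
- Slopes 1 and 0.5: −1.02; 0.01.
- Slopes 1 and 0: −2.06; −0.07.

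The Monte Carlo error is about 1.7/√1500 = 0.04 points. The rule discarded 12-month forms from 23.7% to 25.5% of randomised patients; this counts missing baseline forms as well as missing 6-month forms. Bias appears only when the dependence on score differs between arms, and its sign follows the arm with the stronger dependence.

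**The case against.** Several points on the other side deserve weight.

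- **The wording is not airtight.** The rule does not name the 6-month form. It could be a minimum-data rule asking for baseline plus any one later form. Less would then be discarded, though selection would still be on a post-randomisation event. The sequential schedule and the singular noun favour the 6-month reading, but the ambiguity is real.
- **Intention to treat.** A reader might infer a flat contradiction with the Final analysis section. That goes too far: evaluable patients can still be compared by allocated arm. What stands is that a set narrowed by a post-randomisation criterion is not the intention-to-treat population, and the article does not say how the two statements fit together.
- **Size of the loss.** A reader might take 88 to 176 as the expected loss. It is a ceiling. It ignores death, general loss to follow-up and the likelihood that early non-responders miss later forms too.
- **Size of the bias.** A reader might compute a shift in one arm and call it the bias. Suppose 20% of controls have a 30-point deficit, and 30% of them miss the form against 10% of the others. The affected share among completers is 0.14/0.86 = 0.163, and the control mean looks (0.200 − 0.163) × 30 = 1.1 points too good. With the same mechanism and 10% affected in the study arm, the share is 0.07/0.88 = 0.080 and the shift (0.100 − 0.080) × 30 = 0.6, so the net is about 0.5. The documents support none of these inputs, nor a deficit that persists for years.
- **The margin.** A reader might infer that the 5% margin rests on quality of life. The Sample size section cites only the higher morbidity of completion treatment, and part of that morbidity is captured by physician-recorded adverse events, which the rule does not touch.
- **A condensed article.** The choice of model and the handling of missing forms may properly sit in the full protocol or analysis plan. The point does not rest on their absence; it rests on an evaluability rule that the article states.

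**Conclusion.** The point holds. On its most natural reading, the rule excludes patients who miss the 6-month form whatever they return later. It conditions a secondary endpoint on a post-randomisation event and loses usable data.

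The loss is at most 88 to 176 of 878 patients at later visits, with standard errors at most 5% to 12% larger, if 10% to 20% miss the form. Bias is possible, not established: about zero if non-response is unrelated to outcome or related equally in both arms, and roughly 0.9 to 2.1 points on a scale with SD 20 in the illustrative cases where the relation differs by arm. Its direction cannot be stated from the documents. All of this rests on assumed return rates.

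The effect is confined to quality of life and, possibly, the questionnaire part of axillary morbidity. The point should be corrected but does not threaten the trial's main conclusion.

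**What to change.** Replace the evaluability sentence with a rule along these lines: all randomised patients with at least one available questionnaire are analysed by allocated arm, using a likelihood-based repeated-measures model with arm, visit and their interaction.

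Treat the baseline score as part of the outcome vector, or impute it when missing. If baseline enters only as a covariate, patients without a baseline form drop out again, which would undo part of the gain.

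Report questionnaire completion by arm and visit. Keep the baseline-plus-6-month completer set only as a sensitivity analysis, and state how the quality-of-life population relates to the intention-to-treat and per-protocol populations in the Final analysis section.

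The cost is a change of wording and slightly more analysis work, with no new data collection. The model relies on a missing-at-random assumption. In the simulation, the absence of bias with all available forms reflects 12-month return being set unrelated to score, so a sensitivity analysis for data not missing at random would be a sensible addition.
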